**Figure 2 F2:**
[figure not shown]
The flow of health and development resources to the health system.

As Figure 2 shows, financial support for the health sector is rather complex. District health management teams direct the utilization of flexible health accounts, earmarked funds for specific health service activities and earmarked funds for CHPS from external resources. Of the CHPS funding, UNICEF provides support for primary health care equipment and pharmaceutical supplies. This support enables UER districts to equip nurses for community-based health care operations. Of the $0.85 GEHIP provides per capita per year to DHMT. About half of this is earmarked for CHPS start-up activity while half is used to supplement the common fund (“A” in Figure 2). DiHPART facilitates the allocation of flexible funds that are received from the UER-RHA, the Ministry of Health, and GEHIP (“B” in Figure 2). Most funds that are available for CHPS are earmarked for equipment or for supporting ongoing community-based service activities, with no funding available from the health sector for start-up activities such as CHPS facility construction (“C” in Figure 2). However, DiHPART has mobilized the financial commitment of the district development sector to CHPS. This, in turn, has fostered district development investment in CHPS construction and procurement (“D” in Figure 2). This expanded resource for CHPS start-up costs has addressed the critical gap in health financing in GEHIP treatment districts and it explains their rapid implementation of CHPS and the outcomes associated with community-based primary health care (“E” in Figure 2).

DiHPART has also become a tool for demonstrating the value of district development investment in CHPS. Prior to DiHPART, district managers lacked revenue for starting CHPS operations and practical tools for interacting with local politicians and development officers who had control of development resources for bridging funding gaps. The toolkit helped GEHIP district teams interact with counterparts with simple to understand visual diagrams of the value of health investment. The combination of leadership demonstration activities, community interaction, and DiHPART demonstrate the value of CHPS on scale-up in the three project districts, as Figure 3 shows. In 2009, coverage of CHPS in treatment districts was lower than in comparison districts. Today, after two years of GEHIP, coverage in treatment districts is now reaching 68% of the population, or roughly double the level of coverage in comparison districts. Indeed, projecting the rate of change in coverage suggests that GEHIP will have completed the scale-up process within another year in treatment areas; total coverage, however will require over six years of effort in comparison areas at the present rate of progress. Clearly, the combined effects of leadership training, catalytic investment, political engagement, and evidence-based budgeting are solving the CHPS start-up problem.

**Figure 3 F3:**
[figure not shown]
Time trend in the percent of the population reached by CHPS services in GEHIP treatment and comparison districts, January 2006-June 2012.

## Evaluation design

Both quantitative and qualitative research methodologies will be used to evaluate the impact of GEHIP.

### 

#### Assessing impact

To adequately power the sample for unbiased estimates of posited changes in child survival, it is estimated that a total sample size of 5,741 women is required. However, assuming response/attrition of 10%, GEHIP increased the planned sample size to 6,300 respondents to ensure an adequate analysis base despite possible sample loss. GEHIP controls for baseline differences in background characteristics with “difference-in-differences” estimates of program impact [19] as the average treatment effect (ATE) given by:

Y describes a health outcome such as the under-5 mortality rate or another of the indicators appearing in Table 1, the subscript *t* refers to measurements of health outcomes at baseline, t′ refers to measurements of health outcomes at the end of the project, G indexes GEHIP localities, and C indexes comparison localities.

**Table 1 T1:** Core Maternal, Newborn and Child Health Impact Indicators

Category	Indicator
**Mortality rates (by gender of child)**	• Neonatal mortality rate • Infant mortality rate • Under-5 cumulative mortality rate (q5 ) • Estimated under-5cause specific mortality rate for malaria, acute respiratory infections

**Maternal Health Behavior (last live birth)**	• Percent of women who made their first ANC visit before the fourth month • Percent of pregnant women who attended four or more ANC visits • Percent of pregnant women who attended postnatal care visit • Percent of women who deliver in a health facility • Proportion of C-sections among last born.

**Newborn Health**	• Percent of newborns attending postnatal care visits • Percent of newborns breastfed within 1 hour of birth • Percent of women that report having practiced at least three ENC behaviors

**Under-5 child health**	• Percent episodes of diarrhea in children under 5 treated with ORS + zinc • Percent episodes of cough/pneumonia in children under 5treated with antibiotics • Percent of febrile malaria episodes among children under five treated within 24 hours of onset

**Family planning and fertility**	• Contraceptive prevalence rate • Unmet need for family planning • Age specific and total fertility rates

Data from the household surveys on health status can be linked to facility data and health system readiness checklists to allow the project to determine whether changes in health outcomes are attributable to health systems processes. Multilevel hazard models of under-5 survival in the 60 sample GEHIP clusters will permit estimation of the effect of health system strengthing on child survival, adjusting for the potentially confounding effects of household characteristics.

If GEHIP replicates the full effect of the Navrongo model, then its success in scaling up CHPS will reduce childhood mortality by half in three years.

A limitation of the impact evaluation strategy is the timing of the endline survey, scheduled for mid-2014. To gauge the full impact of the Figure 3 CHPS coverage success, the survey should be conducted approximately three years after July 2013, when coverage will be complete. While results of a survey in 2014 may establish statistical significance of results, the more important question concerns the potential impact of achieving a new global goal for impoverished rural settings: “University Health Coverage” comprised of doorstep primary health care for all, comprehensive preventive health services, cost-free emergency referral, and care for mothers and children.

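### At the stated 10% loss, 6,300 women leave 5,670, which is 71 (1.2%) below the 5,741 said to be required: a minor error in the stated figure

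*Protocol article*

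**What the plan says.** The article's only sample-size statement stands at the start of Assessing impact, under Evaluation design. It gives three figures in two consecutive sentences.

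- Requirement: "it is estimated that a total sample size of 5,741 women is required".
- Loss allowance and planned size: "assuming response/attrition of 10%, GEHIP increased the planned sample size to 6,300 respondents to ensure an adequate analysis base".
- Stated purpose of the increase: "to ensure an adequate analysis base despite possible sample loss".

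The article does not give the inflation formula. It also does not say whether the 6,300 are women approached or women interviewed, or whether the figures apply to each survey round or to baseline and endline together.

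**The concern.** An allowance for loss has one job: after the assumed loss, the number left should be at least the number required. Here the requirement, the loss rate and the inflated number are all printed, so the claim can be checked without any outside input. At the article's own loss rate it fails. The full protocol could explain how 6,300 was chosen, but it could not make a 10% loss from 6,300 leave 5,741.

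What is at stake is the accuracy of the statement that supports the child-survival comparison. Anyone who audits or reuses the figure would take 6,300 as sufficient at 10% loss, and it is not quite sufficient.

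**Working it through.** **Inputs, all from Assessing impact:** required n = 5,741; loss d = 0.10; planned N = 6,300. N is taken as the number before loss.

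**1. Can the plan's own 6,300 be reproduced?**
- Add-on formula, n × (1 + d): 5,741 × 1.10 = 6,315.1. The planned figure is about 15 women lower.
- Division formula, n / (1 − d): 5,741 / 0.90 = 6,378.9, so 6,379. The planned figure is 79 lower (79 / 6,300 = 1.25%).
- Increase actually made: 6,300 − 5,741 = 559, and 559 / 5,741 = 9.7%.

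Neither formula gives 6,300 exactly. The closest explanation is a 10% add-on rounded down to a round number. That is an inference, because the article does not state its method. The add-on formula is itself not the right one, since 10% of the larger number is lost and not 10% of the smaller.

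**2. What is left after the stated loss?**
- N × (1 − d) = 6,300 × 0.90 = 5,670.
- Shortfall: 5,741 − 5,670 = 71, and 71 / 5,741 = 1.2%.

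**3. How much loss does 6,300 tolerate?**
- 1 − 5,741 / 6,300 = 559 / 6,300 = 8.87%.

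**4. What would the shortfall cost in power?** The article gives neither alpha nor power, so the following are assumptions: two-sided alpha 0.05, power of 80% or 90% at n = 5,741, and precision proportional to the square root of the number of women. With Φ the standard normal distribution function,

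power at 5,670 = Φ[(1.96 + z) × √(5,670 / 5,741) − 1.96],

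where z is 0.842 for 80% and 1.282 for 90%.

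| Power assumed at 5,741 | Power at 5,670 |
|---|---|
| 80% | 79.5% |
| 90% | 89.6% |

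The cost is half a percentage point or less. In a clustered sample, losing a few women within each cluster reduces the effective sample less than proportionally, so these figures tend to overstate the cost.

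**5. The other reading of the planned size.** If 6,300 counts completed interviews, loss has already been taken off. The analysis base then exceeds the requirement by 559, and steps 2 to 4 do not apply.

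**The case against.** The strongest reply is that this is rounding. The requirement is itself an estimate, 10% is a round assumption, and an increase of 9.7% rounds to 10%. A planning allowance is not meant to be exact to the woman, and an actual loss of 8.87% or less removes the gap. Most of this stands, and it is why the point is minor. It does not make the sentence correct. The requirement is printed to the single woman, and rounding an allowance for loss downwards works against its purpose.

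The second reply is that respondents may mean completed interviews, in which case nothing is short. The article does not settle this. The wording points the other way: the size was raised because loss was assumed, and the aim was to keep an adequate base "to ensure an adequate analysis base despite possible sample loss". That describes a number before loss. If completed interviews were meant, the sentence still needs a word to say so.

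A reader might infer two stronger things, and the documents support neither.

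- **That the study is underpowered.** The article gives no alpha, power, detectable effect or design effect, so the power behind 5,741 cannot be recovered. Under conventional assumptions the shortfall moves power by half a point or less.
- **That a few more women per cluster at endline would repair it.** That needs the allocation across clusters, which is not given. It is also not settled that "Multilevel hazard models of under-5 survival in the 60 sample GEHIP clusters" cover both intervention and comparison areas. The design compares baseline with endline, the article writes of baseline in the past tense, and women added at endline would not restore a shortfall at baseline.

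**Conclusion.** The point holds as a minor error, wrong as written. Taking 6,300 as the number before loss, the plan's own 10% leaves 5,670 women, 71 (1.2%) below its own requirement; full inflation is 6,379. The arithmetic rests only on printed figures and on that reading of the planned size, which the wording favours but does not prove. The power figures rest on an assumed two-sided alpha of 0.05 and an assumed starting power, and they show a negligible effect. Nothing here calls the design, the analysis or the feasibility of the comparison into question.

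**What to change.** Any one of the following is enough, depending on what was meant:

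- **Keep 6,300 and restate what it achieves.** Say that it meets 5,741 only if loss is at most about 8.9% (8.87%), and that it yields 5,670 at 10%. This costs one clause and no fieldwork.
- **Correct the inflated target to 6,379,** shown as 5,741 / 0.9. This costs one number in the text. If the larger target were also to be fielded, it means 79 more women, and the plan would have to say in which survey round or rounds.
- **If 6,300 means completed interviews, say so.** Then the base already exceeds 5,741 and only the wording changes.

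The first option is the simplest and is proportionate to a 1.2% gap.

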#### Assessing organizational context, inputs, processes, and outcomes

The quality of administrative data and HMIS may be improved by GEHIP activities, resulting in spurious changes in health systems indicators in intervention districts relative to comparison districts. For example, drug shortages may appear to be more common in intervention areas not because they are actually increasing but because facilities in intervention areas are better equipped to report such shortages. To account for this possibility, the project conducts recurrent facility surveys in intervention and comparison localities at all levels of care, including CHPS compounds.

GEHIP monitors systems inputs and outputs and processes in intervention and non-intervention areas through administrative data collection, HMIS, qualitative appraisal, and facility-based surveys. The project will also rely on the CHPS monitoring database, a tool for documenting the national state of CHPS implementation.

GEHIP has adapted procedures that were developed for the qualitative appraisal of CHPS implementation to the study of GEHIP implementation [20]. Focus groups and in-depth interviews are conducted among community stakeholders, frontline workers, supervisors, and district managers. To facilitate process documentation, a knowledge management scheme compiles qualitative data and narrative summaries of project implementation experience, problems that arise, and implementation lessons that are learned. A series of journalistic notes has been launched to capture salient episodes from this experience [21].

#### Other contextual factors

Activities in both the intervention and non-intervention districts are occurring which the project lacks control. For instance, all three northern regions of Ghana are target districts for interventions by UNICEF and other donors. Since these priority interventions will take place in both treatment and comparison districts, donor priorities may contaminate the GEHIP intervention. GEHIP collects contextual information on external activities that may impact the primary outcomes of interest. Of particular significance is the recent parliamentary decision to split districts into smaller political units. At the onset of the project, there were nine functioning districts; by mid-2013 there will be 13. Data compiled from each sample cluster will include indicators of exposure to investments of external agencies and indicators of changes in political boundaries so that multilevel analyses can adjust for their potentially confounding effects and exposure to project interventions is appropriately attributed to sample survey clusters.

#### Economic evaluation

Economic evaluation of the project will assess the unit cost associated with net health benefits that accrue from GEHIP expenditures. Cost and expenditure data are being gathered at each level of the system to allow for estimation of benefits resulting from supplementary expenditures in intervention districts. Efforts are directed to assessing external investment in regional programs, with particular attention to expenditures of UNICEF and other international agencies.

## Implementation challenges and lessons learned

Table 2 summarizes challenges to the effective provision of primary health care in rural areas of Ghana and GEHIP implementation lessons about feasible strategies for addressing them. At baseline, neonatal and maternal mortality rates were unacceptably high, but the rapid training of frontline workers proved to be inexpensive, operationally feasible, and potentially effective in reducing maternal and neonatal mortality. Moreover, a pilot referral system utilizing tri-car ambulances has been implemented in one GEHIP district and information systems have been reformed through the adoption of the simplified register system.

**Table 2 T2:** GEHIP PHIT implementation progress: success, challenges, adaptations.

***Successes***
***Development of a toolkit for budgeting and finances.*** With technical assistance from the University of Dar es Salaam Computing Centre and the Ifakara Health Institute, GEHIP re-engineered Tanzania’s PLANREP budgeting toolkit for Ghana. This involved utilizing Navrongo Health Research System generated burden of disease data and Government of Ghana accounting procedures to develop a model for translating budget plans into visualized data on their burden of disease implications: The District Health Planning and Reporting Toolkit (DiHPART). ***Development of simplified HMIS data capture and data utilization procedures*** GEHIP provided direct support to a reform of the national “District Health Information Management System Version-2” by providing community-level components of the reformed system. This involved streamlining registers, testing their application, revising content, and developing feedback tools, data visualization, and supervisory leadership mechanisms for improving the use of HMIS for decision-making. ***Mortality auditing.*** All frontline workers have been trained to produce simple-to-interpret narrative reports on all known maternal and neonatal deaths. A medical review panel has been constituted to conduct weekly reviews of these audits. ***Training of frontline workers in emergency management*** All frontline workers were trained to refer deliveries and care for newborn needs. Missing elements of emergency management were identified by GEHIP mortality audit scheme with training instituted in response to problems. ***Improved collaboration and co-financing of community based primary health care by district and local government.*** All district managers were trained in CHPS implementation and equipped to use DiHPART for orienting district political leaders to the benefits of CHPS investment. Improved understanding of the health benefits of CHPS has catalysed incremental funding for implementing community-based care. CHPS coverage accelerated as a consequence.

**Challenges**

***DiHPART.*** Trial of the system demonstrated that categories used for data visualization are inconsistent with decision-making options. Also, changes in the national accounting system are not yet reflected in the DiHPART tool. DiHPART requires re-engineering based on lessons learned. ***Cash flow and planning***. DiHPART assumes that the district level common fund is available for managers to allocate according to plans. Long delays in the allocation of Common Fund revenue challenge that assumption. Actual expenditure patterns differ from budget parameters because of unpredictable flow of essential revenue. ***Fidelity to proven operational models.*** Implementation of the National Health Insurance System (NHIS) has dysfunctionally shifted the focus of care to clinic-based services, detracting from outreach and operational strategies that have been proven to work. ***Excess mortality*** Audits have revealed excess neonatal mortality from asphyxia, and maternal mortality from convulsions, and haemorrhaging. ***Effective supervision at the community level.*** Research shows that supervisory field encounters are the main factor affecting community health worker performance. However, NHIS reimbursement policies reimburse supervisory staff for clinical services rendered. Supervisory field work has diminished. ***Timing of Systems Changes.*** As Figure 3 shows, GEHIP has taken time to implement: changing the leadership system, accelerating the flow of resources from the development sector, and the implementing community health services has taken 18 months of project time that impacted on CHPS coverage in project Years 2 and 3. The full child survival impact of GEHIP will be realized well after the project is completed.

**Adaptations**

***DiHPART.*** While DiHPART was conceived as a resource allocation tool, its value to GEHIP has shifted somewhat to resource development. Visualizing the health benefits of investment in CHPS has facilitated district dialogue about ways for development revenue to bridge critical resource gaps. The absence of budget lines for CHPS start-up costs prevents the expansion of community-based primary health care, leadership training, field demonstration, and DiHPART have been combined into a paradigm for multi-sectoral investment in CHPS expansion. ***Excess mortality.*** High neonatal and maternal mortality from preventable causes has fostered strategic planning about training needs, referral systems development, and information systems reform. Research findings and plans have been translated into fund-raising initiatives that are successfully augmenting GEHIP with resources for addressing excess mortality. ***Fidelity to proven CHPS strategies.*** GEHIP has been a mechanism for systems diagnosis, documentation, and national dialogue about implementation lapses in the national CHPS program. Simple to implement corrective measures that are instituted by GEHIP are developing treatment districts into a national learning platform for health systems development. The UER, in turn, is becoming a learning region for guiding national strategies for achieving universal health coverage, accessible care, and comprehensive community health services. ***Timing of Systems Changes.*** The national CHPS monitoring system lapsed in 2008 with the conclusion of external funding arrangements. In response, GEHIP has developed reformed CHPS coverage monitoring tools that enable the project to conduct longitudinal observation of the scale-up of CHPS implementation (as illustrated by Figure 3). New monitoring tools, integrated into DHIMS-2, will enable the GHS to have real-time access to information about systems development progress and lapses.

The GHS PPME Division has committed to merge the simplified GEHIP registers with its new DHIMS-2 system and then scale the combined system up nationally, once technical problems with the existing tool are resolved.

Implementation research has also been crucial to the process of scaling up. For example, problems arose during the piloting of the ambulance based emergency referral program described above. A bilateral donor provided Ghana with several hundred fuel efficient three-wheel “tri-cars,” several of which the GHS consigned to GEHIP for the pilot trial. However, tri-car ambulances designed for Asian urban conditions were highly unsuitable to the terrain of northern Ghana. Problems also arose during a trial of procedures for organizing and streamlining communication between remote health posts, sub-district health centers, and district hospitals using mobile phones. The study itself was successful but [22] advanced engineering “m-health” concepts, involving the extension of automated voice communication to mothers, was found to be less effective than simple-to-implement face-to-face voice communication between mothers and health workers [23,24].

GEHIP has encountered other problems with DiHPART implementation. The tool assumes that “interventions” are grouped by disease syndromes or broad categories of activities that are complex, involving a wide range of investment options of varying degrees of efficacy or efficiency. IMCI, for example, is a complex array of community, clinical, and hospital-based activities. Disaggregating IMCI as a DiHPART parameter would assist DHMT in determining which IMCI investments make the most sense, given the resource environment. In revised form, DiHPART would visualize the burden of disease implications of more detailed health expenditure options.

DiHPART implementation within districts has also proven to be challenging, owing to persistent staff turnover and hardware issues. Analysis of output from DiHPART has been compromised by software limitations, including its inability to provide for the management of actual cash flow. The lack of expenditure tracking capabilities impedes the administrative requirement of comparing actual spending to the planned budget. While district managers utilize DiHPART to plan activities, the system is not yet an accounting tool. As these issues are resolved, the tool is likely to be used at national and regional levels, enabling health plans to be based on scientific evidence and, therefore, more effective.

